## Abstract

**Background:**

Depression is a common and disabling condition. In Chile, assistance is guaranteed by law through a national program for depression in primary care services, and there is evidence of effective treatment for depressed women. However, there is a shortage of evidence-based treatments for depression in adolescents. The incorporation of technology to expand therapeutic options is becoming more common. This proposal aims to compare the efficacy of therapy that enhances traditional face-to-face cognitive-behavioral therapy (CBT) with a computer-based program versus usual care to treat depression in adolescents in primary care clinics in Santiago, Chile.

**Methods and design:**

This is a two-arm, single-blind, randomized controlled trial with a target enrollment of 216 depressed adolescents between 15 and 19 years of age, attending four primary care clinics in Santiago, Chile. In the active arm, depressed adolescents will receive eight sessions of computer-assisted CBT, led by trained psychologists on a weekly basis. In the control arm, depressed adolescents will receive treatment as usual from the primary care centers. Mean depression scores and indicators of dysfunctional thoughts, problem-solving strategies, and health-related quality of life will be measured at baseline and four and six months after randomization.

**Discussion:**

As far as we know, this is the first randomized controlled trial of a computer-assisted CBT intervention for depressed adolescents in a Latin American country.

**Trial registration:**

Clinical Trials: NCT01862913

## Background

Depression is a global public health concern, as it is a highly prevalent and recurrent condition that affects people of all ages and carries high individual, family, and social costs
[1]. It is currently a leading cause of burden worldwide, measured in terms of disability-adjusted life years
[2].

Key epidemiological studies have investigated the burden of depression in the Chilean general population
[3, 4], and in recent years, research has reported a high prevalence of depression in adolescents between the ages of 12 and 18
[5].

To address the needs of the population, a National Depression Detection and Treatment Program in Chilean Primary Care was first introduced in 2001, consisting of a stepped care program that combines medical and psychosocial interventions, as well as improved detection, diagnosis, treatment, and follow-up of each case
[6, 7]. In 2006, the treatment of depressive episodes, recurrent depressive disorder, and depressive episodes of bipolar disorder was strengthened with the introduction of the Regime of Explicit Health Guarantees (AUGE)
[8]. This plan ensures access to opportune, quality, and financially protected depression treatment for all persons 15 years of age and older. In this plan, the primary care teams play a leading role in the management of depression. The AUGE Clinical Guidelines for Depression treatment in primary care include pharmacological treatment, medical controls, psychosocial interventions, and referral to secondary or tertiary psychiatric services, depending on the specificities of each case
[9]. Additionally, it is important to note that, in Chile, there is evidence of effective psychosocial treatments based in primary care centers for depressed low-income women and for mothers affected by depression during the postnatal period
[10, 11].

International studies have shown that adolescent depression is strongly linked to clinical and social morbidity
[12, 13]. However, although several systematic reviews have demonstrated the efficacy of cognitive-behavioral therapy (CBT) interventions
[14, 15], there has been little or no research into adolescent depression treatment options in Chile. One way to increase the appeal of CBT for adolescents could be to use computer-assisted therapy. This is especially important in primary care centers where CBT for adolescents with depression in routine clinical practice is limited
[16]. Eells *et al.* define computer-assisted psychotherapy as a ‘psychosocial treatment in which a significant portion of the content is delivered with the use of computer technology or in which the computer technology assists the work of a therapist’
[17]. The incorporation of technology to expand therapeutic options is becoming more common. Computer-based or online programs have proven efficacy in the treatment of adults
[18, 19], although the outcomes in adolescents remain unclear
[20]. A pilot study has shown that adolescents could be motivated by the incorporation of technology into therapeutic sessions at their homes, guided by a professional who is not a CBT therapist, though the sample size of this study is quite low
[21]. There has yet to be a randomized controlled trial to evaluate a procedure that enhances traditional face-to-face CBT with a computer program for adolescents in primary care centers.

Adding a computer-based component to face-to-face psychotherapy sessions may further favor the acceptance and incorporation of CBT therapy techniques. This combination would take advantage of the strengths of each approach: (1) the multi-media program could better hold the attention of the adolescents, while providing them with more stimuli and therefore an enhanced learning experience; and (2) the presence of a clinician permits the development of a therapeutic bond and allows for the tailoring of the program to the individual case. Furthermore, a systematic review and meta-analysis found that when computer-assisted therapy was combined with clinician support, the dropout rate was significantly lower than it was for programs without the presence of the therapist (28% versus 74%)
[18]. For these reasons, we believe that the use of a computer-assisted CBT program, delivered in person by trained therapists, is a promising way to deliver these treatments among adolescents.

## Methods and design

This is a two-arm, single-blind (blinded only to outcome assessor), individually randomized controlled trial, which will compare the efficacy of computer-assisted CBT versus usual treatment for depression in adolescents in primary care clinics in Santiago, Chile.

### Aims and hypotheses

#### General aim

To carry out a randomized controlled trial to compare the efficacy of a computer-assisted CBT intervention versus usual care to treat depression in adolescents in primary care clinics in Santiago, Chile.

#### Specific aims

To compare the level of depressive symptoms of adolescents suffering depression treated with computer-assisted CBT versus usual care in primary care clinics.To compare the level of dysfunctional thoughts, strategies for solving problems, and health-related quality of life (HRQoL) of adolescents suffering depression treated with computer-assisted CBT versus usual care in primary care clinics.To compare adolescents’ adherence to computer-assisted CBT versus usual care in primary care clinics.To compare adolescents’ satisfaction with computer-assisted CBT versus usual care in primary care clinics.

#### Hypotheses

Adolescents receiving the intervention will achieve lower scores (difference in mean of at least 0.4 standard deviations) in the depression questionnaire than those receiving the usual care, four months after randomization.Adolescents receiving the intervention would have fewer dysfunctional thoughts than those receiving the usual care, four months after randomization.Adolescents receiving the intervention would be better at solving problems than those receiving the usual care, four months after randomization.Adolescents receiving the intervention would have better HRQoL than those receiving the usual care, four months after randomization.Symptomatic improvements achieved at four months after randomization will be maintained at six months after randomization.

### Setting and population

Adolescents between 15 and 19 years of age attending four primary care clinics located in Puente Alto, a low-income municipality of Santiago, Chile, with a large adolescent population.

### Inclusion and exclusion criteria

Depressed adolescents aged between 15 and 19 years of age will be invited to participate. Informed consent will be obtained from each participant over 18 years of age, and from the parent or guardian of under-age participants. In the case of the latter, informed assent from the participants will also be required to continue with the study. Depression will be assessed with the Beck Depression Inventory (BDI)
[22]. Adolescents scoring ten or more points on the BDI will be invited to a semi-structured diagnostic interview that includes the Kiddie-SADS-Present and Lifetime Version interview (K-SADS-PL)
[23] to assess other inclusion criteria (diagnostic criteria for depressive disorders) and to ensure that they do not meet the exclusion criteria (current suicidal risk requiring in-patient care, current psychosis, alcohol or substance dependence, or low intellectual ability). Those taking antidepressants or receiving psychotherapy, and those with a history of bipolar illness, will also be excluded. The K-SADS-PL interview will be conducted with all potential participants by the principal investigator (VM), who is a child and adolescent psychiatrist, or a clinical psychologist, who have both been certified in conducting the interview.

### Training of primary care center professionals

Before the start of recruitment, professionals in the four participating primary care centers will receive a special training session from the principal investigator (VM) to assist with the correct identification, diagnosis, and treatment of patients with depression, according to the AUGE Clinical Guidelines for Depression. There will also be a refresher session 6 months after the start of recruitment.

### Intervention arm

The intervention arm will receive eight sessions of computer-assisted CBT plus usual medical treatment, as described in the AUGE Clinical Guidelines for Depression. Computer-assisted CBT sessions will be delivered on a weekly basis and assisted by trained psychologists in face-to-face meetings. The program is called ‘Yo pienso, siento y actúo mejor’ (YPSA-M); in English, ‘*I think, feel, and behave better*’. Topics covered in the program will include information on symptoms and causes of depression, treatment options, problem-solving techniques and other cognitive-orientated strategies to challenge negative thoughts. Copies of the computerized program are available upon written request to the principal investigator (VM).

Psychologists delivering the intervention will receive 12 hours of training and will be supervised by the study principal investigator (VM) once a month, and upon request.

Between sessions, members of the study team will contact the participants to remind them of upcoming appointments in the intervention arm.

### Control arm

The control arm will receive treatment as usual from the primary care clinics. The professionals in the primary care centers will be instructed to follow the AUGE Clinical Guidelines for Depression.

### Outcome measures

#### Primary outcome measures

Depressive symptoms will be assessed as a primary outcome using the BDI as a continuous variable. This inventory is designed to evaluate depressive symptoms in adults and adolescents from the age of 13. The BDI is a brief and well-established depression questionnaire translated into different languages and used widely throughout the world. It has shown good psychometric properties
[22]. It has previously been used in primary care settings in Chile
[24].

#### Secondary outcome measures

The Children’s Automatic Thoughts Scale is a self-reporting questionnaire to evaluate dysfunctional thoughts of children and adolescents. Internal consistency of the subscales is high, and the test-retest reliability is adequate
[25]. The ‘personal failure’ subscale will be used as a secondary outcome measure. This subscale was chosen because it is most closely associated with depression. It has ten items. Each item is given a score of between 0 and 4 points and thus the total score varies between 0 and 40. Highest scores show a greater presence of negative automatic thoughts. In the validation study, this subscale discriminated well between the community sample and the sample of depressed individuals; the Cronbach’s alpha coefficient was 0.92. The test-retest correlation coefficient was 0.80 at one month and 0.74 at three months. The mean score in a non-clinical sample was 6.48 (standard deviation = 7.20)
[25].

The Social Problem-Solving Inventory - Revised Short Form is a self-reporting questionnaire with 25 items. It consists of five subscales with five items each. Two of these subscales, ‘positive problem orientation’ and ‘negative problem orientation’, assess functional and dysfunctional cognitive and emotional orientations towards solving problems. The three remaining subscales, ‘rational problem solving’, ‘impulsivity-carelessness style’, and ‘avoidance style’, assess problem-solving skills and behavioral style. The total score of this scale varies between 0 and 20 points. Highest scores correspond to better social problem-solving abilities
[26]. Calvete and Cardeñoso
[27] used a Spanish version that had good psychometric properties and had been used in Chile. Cronbach’s alpha coefficient varied between 0.64 and 0.82 in the different subscales
[27].

The KIDSCREEN-27 is a HRQoL questionnaire and consists of 27 items pertaining aspects of the child’s physical wellbeing, mood, autonomy, satisfaction with parental relationship and the atmosphere at home, perceived nature of the respondents’ relationships with other children or adolescents and perceptions of his or her cognitive capacity, learning and concentration, and his or her feelings about school. The KIDSCREEN items assess either the frequency of certain behaviors or feelings (never, seldom, sometimes, often, always) or, in fewer cases, the intensity of an attitude (not at all, slightly, moderately, very, extremely). The recall period is one week. For the scoring and analysis, negatively worded items will be recoded so that for all items, higher scores indicate a better HRQoL
[28]. The KIDSCREEN has been validated in Chile
[29].

### Other outcomes

The attendance of participants in both study arms to programmed appointments will be monitored, to evaluate treatment adherence. Additionally, satisfaction with treatment will be measured with a self-report questionnaire, six months after the baseline assessment.

### Sample size

We anticipate that the intervention, will produce a clinically meaningful improvement (remission) in 60% of adolescents and only 40% of those in usual care will reach this level of improvement in four months. A difference of 20% will be regarded as worth detecting and clinically meaningful. For a two-sided alpha coefficient of 5% and a statistical power of 80%, 97 adolescents will be needed in each group to detect this difference, or 108 subjects per group, allowing for 10% attrition. This total also yields an 80% power to detect a difference in mean of at least 0.4 standard deviations in the primary outcome measure.

### Recruitment

Adolescents eligible for the study will be identified by health professionals of the four primary care clinics, as well as by psychologists and counselors of nearby schools, who will be informed of the study, trained to identify potential cases of depression among their students, and instructed to refer any adolescent who seems to have depression symptoms to the primary care clinics for further evaluation and possible participation in the study, according to inclusion and exclusion criteria.

### Group assignment

Those adolescents who at baseline assessment meet the inclusion criteria and do not meet the exclusion criteria will be randomly assigned to the intervention arm or to the control arm. Blocked (size of four), stratified randomization will be used. Stratification will be implemented regarding sex and severity of depression (mild, moderate, and severe) according to BDI score. Randomization will be generated using web-based random allocation algorithms. Allocation concealment will be carried out by keeping treatment assignment in numbered sealed envelopes in a central place; the envelopes will be opened by individuals who do not participate in the recruitment process.

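### One disclosed block size of four, in a trial where an eligibility interviewer may also supervise the CBT therapists, leaves up to a third of assignments inferable from earlier ones

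*Protocol article*

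**What the plan says.** All references are to the protocol article.

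- **Sequence** (Group assignment): "Blocked (size of four), stratified randomization will be used". No second block size is mentioned.
- **Strata** (Group assignment): "Stratification will be implemented regarding sex and severity of depression (mild, moderate, and severe) according to BDI score". That is 2 × 3 = 6 strata. Clinic is not a stratification factor.
- **Concealment** (Group assignment): "Allocation concealment will be carried out by keeping treatment assignment in numbered sealed envelopes in a central place", and "the envelopes will be opened by individuals who do not participate in the recruitment process".
- **Blinding** (Methods and design): the trial is described as "single-blind (blinded only to outcome assessor". No other party is said to be blinded.
- **Eligibility** (Inclusion and exclusion criteria): "The K-SADS-PL interview will be conducted with all potential participants by the principal investigator". The sentence goes on to allow a clinical psychologist as the alternative, and both are certified. The BDI score has already been taken, because a score of ten or more is the gateway to this interview.
- **Supervision** (Intervention arm): the psychologists who deliver CBT "will be supervised by the study principal investigator", monthly and on request.

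**The concern.** With a single known block size, the end of each block is a matter of counting. Once two participants in a block of four have gone to one arm, the rest of that block is fixed. Counting needs three things: the stratum, the order of enrolment within it, and the earlier allocations. Sex and BDI severity are available at the interview. Treatment is open to everyone except outcome assessors, and one of the two possible interviewers has a supervisory role that could bring knowledge of who is in the CBT arm. Control status could then be inferred from absence from the CBT caseload.

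At stake is selection bias at entry. Some criteria need judgement: the diagnostic threshold, suicidal risk of a degree that calls for in-patient care, substance dependence and low intellectual ability. If those calls were coloured by the expected arm, the groups could differ on traits that are not measured, such as motivation. Stratification would not balance such traits and baseline adjustment would not correct them. The primary outcome is a self-reported BDI completed by unblinded participants, so an unpredictable sequence is one of the main protections this trial has.

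**Working it through.** **Inputs.** Fixed block of four (Group assignment). Six strata (Group assignment). Two per arm in each block, taking 1:1 from the equal group sizes under Sample size: "97 adolescents will be needed in each group to detect this difference, or 108 subjects per group, allowing for 10% attrition". Total 2 × 108 = 216.

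**The plan's own figure.** The article gives no figure for predictability, so only the total can be reproduced. For 60% versus 40%, two-sided 5%, 80% power and pooled variance under the null:
n = [1.960 × √(2 × 0.5 × 0.5) + 0.842 × √(0.24 + 0.24)]² / 0.20² = (1.386 + 0.583)² / 0.04 ≈ 97 per group.
97 / 0.9 = 107.8, so 108 per group and 216 in all. This agrees with the article.

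**Certain assignments, fixed block of four.** There are six equally likely orders: AABB, ABAB, ABBA and their mirror images.
- AABB type: positions 3 and 4 are determined (2).
- ABAB and ABBA types: only position 4 is determined (1 each).
- Mean: (2 + 1 + 1) / 3 = 4/3 per block. Share: (4/3) / 4 = 33.3%.
- 216 × 1/3 = 72 if every block fills. Simulating 216 participants in six strata with incomplete last blocks gives about 32%, or roughly 70.

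**Best guess, always naming the arm that is behind.**
- Position 1: 1/2.
- Position 2: 2/3.
- Position 3: (1/3) × 1 + (2/3) × (1/2) = 2/3.
- Position 4: 1.
- Sum 17/6. Share: (17/6) / 4 = 17/24 = 70.8%, or about 70% with incomplete last blocks. Chance is 50%.

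Both results assume that every earlier allocation in the stratum is known at once.

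**With less knowledge.**
- Only the overall imbalance known, not the stratum: about 59% of guesses are correct (simulation).
- Allocations learned only at month end, the one regular supervision interval stated. The recruitment period is not given, so 12 to 24 months is assumed, with equal or unequal strata. Certain assignments fall to roughly 11% to 19% (about 23 to 40 participants) and correct guesses to 58% to 63%.
- A further week before a case becomes visible: roughly 6% to 14% certain and 55% to 61% guessed.

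**With randomly varying block sizes**, even if the interviewer knows the set of sizes:
- Certain assignments (simulation): about 5.5% for sizes 4 and 6, and about 2% for sizes 4, 6 and 8.
- Best guess, from the single-block results 17/24 (four), 41/60 (six) and 373/560 (eight), weighted by participants:
  - 4 and 6: (2.833 + 4.100) / 10 = 69.3%.
  - 4, 6 and 8: (2.833 + 4.100 + 5.329) / 18 = 68.1%.

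The guess rate barely moves because the arm that is behind is still the better bet whatever the block size. What varying sizes remove is certainty.

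**The case against.** The case against is substantial, and much of it stands.

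- **The investigator is not the sole judge of eligibility.** A certified clinical psychologist may do the interview, and the split between the two is not stated. A reader might infer that one person decides all eligibility while watching the allocations. The article does not say that.
- **Knowledge of allocations is inferred.** Supervision is described only by its frequency. Nothing says that the supervisor sees a complete, timely and named caseload. Tracking a block would also need control allocations and the enrolment order in each of six strata, including cases seen by the other interviewer.
- **The one third and the 71% are ceilings.** A reader might take them as expected values. With the monthly delay and assumptions above, they fall to 11% to 19% and 58% to 63%. On-request supervision could raise these, but its frequency is unknown.
- **The safeguards are real.** Envelopes are central, sealed and opened outside recruitment. Clinic and school staff identify candidates. The BDI cut-off and the exclusion of current antidepressants or psychotherapy leave little discretion, and the diagnostic interview is semi-structured.
- **Adjustment can help in part.** Selection acting through measured baseline severity would be partly handled by the baseline adjustment that Data analysis allows when imbalance is found. Selection on unmeasured traits would not.

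These points limit the size of the risk without removing it. Envelopes protect the content of the next assignment, but offer no protection against deducing it from those already made. It is also fair to say that fixed blocks of four are a workable design and that the article does not contradict itself here.

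**Conclusion.** The point holds as an avoidable weakness in the design. A single published block size, open treatment and a possible overlap between interviewing and supervising allow inference that the envelopes do not prevent. Its ceiling is one third of assignments certain (about 70 of 216) and about 71% guessed correctly. This assumes 1:1 allocation and full, immediate knowledge of all earlier allocations in the stratum. The likely exposure is lower and cannot be fixed from the article, because the recruitment period, the split of interviews and the detail seen in supervision are not given.

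The documents do not support reading this as evidence that allocation was predicted or acted on, or that concealment is absent. The sample size, the endpoint and the analysis are unaffected.

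**What to change.** Trial status reports that recruitment began in July 2013, so the change can apply only to assignments not yet made.

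1. Generate the remaining sequence in each stratum with randomly varying block sizes, for example 4 and 6, or 4, 6 and 8. Withhold the sizes from anyone who recruits or interviews. Certain assignments fall from 33.3% to about 5.5% or 2%.
2. Because best-guess accuracy falls only from about 71% to about 69% or 68%, also separate the roles where existing staff allow: eligibility should be judged by a certified interviewer who is unaware of past allocations. The article names a second certified interviewer, but does not say whether that person supervises therapists or learns allocations, so this must be confirmed first.

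Recording eligibility before the envelope is opened would add little. The article already assigns only adolescents found eligible, and that order does not prevent prediction from earlier allocations.

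The cost is a new sequence file and envelopes for future blocks, possibly some reallocation of interviews, and slightly looser balance within strata.

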### Data analysis

Data and presentation of the results will be in accordance with CONSORT guidelines for randomized clinical trials, with the primary comparative analysis being conducted on an intention-to-treat basis. Initially, we will conduct descriptive analysis to assess the balance between the two groups. The primary analysis will employ multivariable linear regression to investigate differences in mean symptom scores (primary outcome measure) between groups at four months after randomization, adjusting for baseline outcome variable if imbalances are identified. Sensitivity analysis making different assumptions will be conducted to investigate the potential effects of missing data. Similar analyses will be conducted for the secondary outcome measures.

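### Randomisation is stratified by sex and BDI severity, but the only covariate rule adjusts for baseline if imbalance is seen, so the stratification factors will usually stay out of the primary model and the test will be conservative

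*Protocol article*

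**What the plan says.** Group assignment: "Blocked (size of four), stratified randomization will be used", and "Stratification will be implemented regarding sex and severity of depression (mild, moderate, and severe) according to BDI score". Two sexes by three severity levels give six strata.

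Primary outcome measures: "Depressive symptoms will be assessed as a primary outcome using the BDI as a continuous variable". The severity stratum is therefore cut from the baseline value of the outcome itself.

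Data analysis: "The primary analysis will employ multivariable linear regression to investigate differences in mean symptom scores (primary outcome measure) between groups at four months after randomization", followed by the one covariate rule in the document, "adjusting for baseline outcome variable if imbalances are identified". Neither sex nor the severity stratum is named for the model, and how imbalance would be judged is not stated. The secondary outcomes are to be analysed in a similar way.

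Sample size: "For a two-sided alpha coefficient of 5% and a statistical power of 80%, 97 adolescents will be needed in each group", then "108 subjects per group, allowing for 10% attrition", with the same total said to give 80% power for 0.4 SD on the primary outcome.

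**The concern.** Blocking within strata forces the arms to be nearly equal on sex and severity, so differences between strata contribute little to the chance variation of the treatment contrast. A model without those factors still counts that variation as residual error. Its standard error then describes a looser design than the one used: confidence intervals are too wide and the test rejects less often than 5% under the null.

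The conditional rule makes this the likely outcome. It admits baseline BDI only after an event that the randomisation is built to prevent. At stake are the accuracy of the reported precision and some power that the design has already bought.

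**Working it through.** **1. The plan's own figures.** For 60% versus 40%, pooled variance, no continuity correction: n = [1.96·√(2·0.5·0.5) + 0.8416·√(0.6·0.4 + 0.4·0.6)]² / 0.2² = 96.9, so 97 per group. Attrition: 97/0.9 = 107.8, so 108. Power for 0.4 SD: Φ(0.4·√(97/2) − 1.96) = Φ(0.826) = 79.6%. All reproduce, and the comparison of means is sized without adjustment.

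**2. Assumptions not in the documents.** 75% female; baseline BDI normal, cut at ±0.6 SD; sex effect 0 to 0.2 SD; baseline-to-month-4 correlation 0 to 0.6; 10% random dropout from 216.

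**3. How often the condition would be met.** With those cut-points, three categories capture 2·0.2743·1.2149² = 0.81 of the baseline variance. The chance difference in mean baseline BDI between arms then has SD of about √0.19·√(4/216) = 0.059 SD.
- A baseline test at p<0.05 needs a difference of 1.96·√(4/216) = 0.267 SD, about 4.5 of those SDs. It was never met in 10,000 simulated trials per setting.
- A standardised difference above 0.1 occurred in about 11% of runs, and one above 0.05 in about 42%. Type I error under these two rules was still 2.4% to 4.2%.

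**4. Size of the effect, by formula.** With R² the outcome variance explained by the strata, the standard error is overstated by 1/√(1−R²), and type I error is 2·[1−Φ(1.96/√(1−R²))].
- R² 0.05: 2.6% too wide, type I error 4.4%
- R² 0.10: 5.4%, 3.9%
- R² 0.20: 11.8%, 2.8%
- R² 0.30: 19.5%, 1.9%

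A correlation of 0.5 with a 0.2 SD sex effect gives R² = 0.25·0.81 + 0.04·0.1875 = 0.21.

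**5. Size of the effect, by simulation** (six strata, blocks of four; 10,000 null runs and 4,000 runs at 0.4 SD per row; Monte Carlo error of a 5% rate √(0.05·0.95/10,000) = 0.2 points). Sex effect 0, 0.1, 0.2, 0.2 and 0.2 SD in turn.

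| Correlation | Unadjusted model SE / true SE | Ratio | Type I, unadjusted | Type I, strata in model | Power, unadjusted | Power, strata | Power, baseline BDI |
|---|---|---|---|---|---|---|---|
| 0 | 0.1433 / 0.1435 | 1.00 | 5.05% | 4.95% | 80.5% | 80.4% | 80.4% |
| 0.3 | 0.1433 / 0.1377 | 1.04 | 4.26% | 5.05% | 79.3% | 81.7% | 82.5% |
| 0.4 | 0.1434 / 0.1341 | 1.07 | 3.58% | 4.84% | 80.3% | 84.9% | 86.0% |
| 0.5 | 0.1435 / 0.1293 | 1.11 | 2.84% | 5.07% | 81.6% | 87.8% | 90.2% |
| 0.6 | 0.1435 / 0.1233 | 1.16 | 2.40% | 5.00% | 83.3% | 91.4% | 93.4% |

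The simulated ratios lie a little below the formula because dropout and part-filled blocks loosen the balance. Other simulations with different seeds, sex effects (up to 0.3 SD) and sex ratios gave unadjusted type I error of 3.9–4.5% at correlation 0.3, 2.7–3.0% at 0.5 and 2.1–2.4% at 0.6.

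With baseline BDI always in the model and sex left out, type I error was 4.9% to 5.2%.

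**The case against.** **The covariate list may not be closed.** The model is called multivariable, the article is a condensed text, and an analysis plan that is not shown could add the strata. This stands against any claim that the trial will certainly omit them: for sex, that would rest on silence. It does not remove the point, because the article does state a rule for baseline BDI, and that rule makes the main prognostic covariate depend on observed imbalance.

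**For the primary outcome, severity is not simply absent.** It is a categorised baseline BDI and enters whenever baseline BDI does. This stands. Baseline BDI alone nearly restores the test, so the fault lies mainly in the conditional clause and only secondarily in the missing mention of sex.

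**The size is assumed.** The documents give no correlation, sex effect or sex ratio. Entry requires a BDI of at least ten, which restricts the baseline range and may lower the correlation. At 0.3 the effect is small. This stands, and only a range can be given.

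**Planned power is met without adjustment.** This also stands: unadjusted power is 79% to 83% against the planned 79.6%.

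A reader might go further and infer that the benefit of stratifying is lost. It is not: the arms stay balanced and the true standard error does fall (0.129 against a reported 0.1435 at correlation 0.5); only the reported precision fails to credit it. A reader might also want clinic in the model on the same grounds. Clinic is not a stratification factor, so this mechanism does not apply to it.

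**Conclusion.** The point holds as a mismatch between the randomisation and the stated covariate rule. Followed as written, the plan will usually give a primary analysis that ignores the strata. If the strata predict the 4-month BDI, the reported standard error is about 4% too wide at an assumed correlation of 0.3 and about 16% at 0.6, and type I error is about 4% and 2.1–2.4% respectively. With no prognostic value the effect is nil, though some is to be expected when severity is cut from the baseline of the outcome itself.

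The error is conservative. A reader might infer inflated false positives or an underpowered trial; neither follows. The loss is about 2 points of extra power at correlation 0.3 (79.3% to 81.7% with the strata) and up to about 10 at 0.6 (83.3% to 93.4% with continuous baseline BDI), plus intervals of the right width. The direction is firm; the size rests on the assumptions listed.

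For the secondary outcomes the same reasoning applies, since a scale's own baseline need not carry sex or BDI severity. No size was calculated for them, and it depends on associations that the documents do not give.

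**What to change.** In Data analysis, replace the conditional clause with a statement that the primary and secondary models include the baseline value of the outcome, sex and BDI severity, regardless of observed balance. Severity may enter as the randomisation stratum or as continuous baseline BDI. For the primary outcome, continuous baseline BDI serves as both baseline outcome and severity, so only sex is added to it.

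The cost is one sentence and a few degrees of freedom out of about 190 (194 evaluable participants). The sample size, the randomisation and the data collected do not change. If an unpublished analysis plan already fixes these covariates, the article and that plan should be brought into line.
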